### Objectives and Aims

The proposed study has 3 aims involving a total of 224 sedentary urban Black women with asthma.

Aim 1A is to determine the efficacy of ACTION intervention on asthma control. We will test the hypothesis that at 24 weeks, Black women with asthma who receive the intervention will have a greater improvement in asthma control (asthma control questionnaire [ACQ]) compared to women in the education control group (efficacy end point).Aim 1B is to examine the maintenance effects of the ACTION intervention on asthma control at 48 weeks. We will examine the long-term impact of the intervention on asthma control (eg, control and quality of life). We hypothesize the effects of ACTION on asthma outcomes will be maintained at 48 weeks.Aim 2 is to explore the behavioral mediators (eg, self-efficacy, social support, self-regulation, and daily PA levels) and contextual moderators (eg, baseline asthma severity, neighborhood environment, comorbid conditions, and social determinants of health) that contribute to treatment responsiveness. Mediation and moderation analyses will be performed with behavioral mediators and contextual moderators.Aim 3 is to assess the reach and implementation potential of ACTION. Reach will be measured by the number of potential participants (based on the recruitment pool) who are randomized into the study. Implementation potential will be measured using a mixed methods approach to identify important explanatory factors underlying the performance of the intervention components.

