### Study Design

This is a 2-arm RCT enrolling participants at the University of Chicago and the University of Illinois at Chicago in which 224 Black women with asthma will be randomly assigned to an education control group or receive ACTION intervention for 24 weeks (Figure 2). The remaining 24 weeks is the maintenance phase, and participants in the intervention group will receive 1 booster group session at ~36 weeks. Assessments will occur at 0, 12, 24, and 48 weeks.

The primary efficacy end point is a change from baseline to week 24 asthma control as assessed by asthma control questionnaire-6. We hypothesize that ACTION will be superior to education control for improving asthma control by week 24. The 48-week time point is important for examining behavioral mediators, contextual moderators, and maintenance of intervention effects.

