### Data Analysis Plan

Data will be analyzed based on the intent-to-treat principle in this multisite RCT. We will use descriptive statistics to describe the sample by intervention group, and any assumption behind each statistical method will be examined during the analysis. Missing data will be handled by each model’s assumption or by using multiple imputation with a fully conditional specification approach, as appropriate [44]. A 2-sided *P* value less than .05 would be considered statistically significant, and the exact *P* value will be reported. All quantitative analyses will be conducted by using SAS (version 9.4; SAS Institute Inc) and R (version 4.0.2; R Core Team).

The primary research outcome for aim 1A is the differences in ACQ score between baseline and 24 weeks for aim 1A and between baseline and 48 weeks for aim 1B. This will be compared between education control and ACTION intervention groups first using 2 sample *t* test to examine the efficacy and the maintenance effect of the proposed intervention, respectively. Two-tailed statistical tests will be conducted throughout the entire analysis unless specified otherwise. A linear mixed model with a subject-level random intercept then will be built on the same outcome in its original scale having time (12 weeks vs baseline; 24 weeks vs baseline; 48 weeks vs baseline), group (ACTION vs education control), and their interaction as the main factors while adjusting for site, recruitment wave, and any imbalanced confounder [45]. This model will allow us to estimate the efficacy of the intervention through the interaction terms after controlling for confounders and subject dependence. Moreover, any missing data can be handled by this model under the missing at random assumption. The estimated coefficients on the mean scale of the outcome will be reported, along with their SEs, 95% CIs, and *P* values. The similar modeling approach mentioned above using generalized linear mixed models instead will be applied to secondary outcomes (asthma quality of life, health care use, and asthma exacerbations) as secondary analyses.

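### The random-intercept-only mixed model can understate the standard error of the 48-week maintenance effect, because it assumes one variance and one correlation across visits at 0, 12, 24 and 48 weeks

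*Protocol article*

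**What the plan says.** The Study Design section sets the visits: "Assessments will occur at 0, 12, 24, and 48 weeks". The last gap is therefore twice as long as each of the first two.

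Under Data Analysis Plan, the ACQ changes from baseline to 24 weeks (Aim 1A) and to 48 weeks (Aim 1B) are compared between "education control and ACTION intervention groups first using 2 sample" t test. The plan then continues: "A linear mixed model with a subject-level random intercept then will be built on the same outcome". Time enters as categories, "time (12 weeks vs baseline; 24 weeks vs baseline; 48 weeks vs baseline", with group and the group-by-time interaction, adjusted for site, recruitment wave and imbalanced confounders. On the purpose of the model: "This model will allow us to estimate the efficacy of the intervention through the interaction terms". On reporting: "The estimated coefficients on the mean scale of the outcome will be reported, along with their SEs, 95% CIs", together with P values. The same paragraph relies on this model for missing data under missing at random.

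No random slope, other residual structure or robust standard error is named. Objectives and Aims gives the 48-week hypothesis: "We hypothesize the effects of ACTION on asthma outcomes will be maintained at 48 weeks".

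**The concern.** With categorical time, the model fits the visit means freely. The restriction is in the covariance. A single random intercept with independent, constant-variance residuals is compound symmetry, so ACQ at baseline is taken to correlate with week 48 exactly as strongly as with week 12. One pooled residual variance then serves every change from baseline.

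In repeated symptom scores, correlation commonly weakens as visits move apart. If it does so here, the pooled figure is an average over short and long gaps: too large for the 12-week change and too small for the 48-week change. Aim 1B uses the longest gap, so its model-based confidence interval would be too narrow and its P value too small. The same covariance governs how the likelihood borrows from observed visits when week 48 is missing.

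**Working it through.** **Inputs from the article.** 224 women in total; visits at 0, 12, 24 and 48 weeks; a 5% level ("value less than .05 would be considered statistically significant", two-sided); random intercept; categorical time; group-by-time interaction.

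**Assumed, because the article gives no figure.** 112 per arm, SD 1 at every visit, and the within-woman correlations below. The article states no standard error, power or correlation for this model, so there is no figure of its own to reproduce first.

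**Formulas.** With complete data and a saturated group-by-time model, the interaction estimate at week *k* is the difference in mean change. Let V be the true 4×4 covariance of one woman's scores and *n* the number per arm.

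- Variance the model reports: 2·s²·(2/n), with s² = tr[V(I − J/4)]/3. It is the same for all three contrasts.
- True variance: (V₀₀ + V_kk − 2V₀ₖ)·(2/n).
- With equal variances, model SE / true SE = √[(1 − mean ρ)/(1 − ρ₀ₖ)], where mean ρ averages the six visit pairs.
- Actual two-sided error at nominal 5% = 2·[1 − Φ(1.96 × ratio)].

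**Worked example, exponential decay with r = 0.7 per 12 weeks.** The six correlations are 0.7, 0.49, 0.2401, 0.7, 0.343 and 0.49, with mean 0.4939.

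- Model variance per woman: 2 × (1 − 0.4939) = 1.012. SE = √(1.012 × 2/112) = 0.134.
- True variance at week 48: 2 × (1 − 0.2401) = 1.520. SE = √(1.520 × 2/112) = 0.165.
- Variance ratio 1.520/1.012 = 1.50; SE ratio 0.82; actual error 11.0%.

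**Range of assumptions.**

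| Assumed pattern | Model/true SE, week 48 | Error, week 48 | Error, week 24 |
|---|---|---|---|
| Compound symmetry, 0.5 | 1.00 | 5.0% | 5.0% |
| Linear decay, 0.7 (12 weeks apart) to 0.6 (48 weeks apart) | 0.92 | 7.1% | 4.8% |
| r = 0.7-0.9 with 30% visit-level noise | 0.90-0.88 | 7.7-8.3% | 4.8-5.1% |
| r = 0.7-0.9 with 20% visit-level noise | 0.87-0.86 | 8.8-9.3% | 4.8-5.1% |
| r = 0.7, no noise | 0.82 | 11.0% | 5.1% |
| r = 0.8, no noise | 0.79 | 12.3% | 4.8% |
| r = 0.9, no noise | 0.76 | 13.6% | 4.5% |

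At week 12 with r = 0.7, no noise, the SE ratio is 1.30, so that standard error is too large.

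Unequal variance alone (correlation 0.5) matters less and can go either way. The week-48 SE ratio is 0.95 if the 48-week SD is 1.2 times the others, and 1.05 if it is 0.8 times.

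**Check by fitted models.** REML fits, 250 runs per scenario, no true effect. Monte Carlo error is about 1.4 points at 5%.

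- r = 0.7, complete data: mean model SE at week 48 of 0.1345 against an empirical SD of 0.159. Rejection was 9.6% at week 48 and 5.6% at week 24; the t test at week 48 rejected 4.0%.
- r = 0.7, with 20% missing at week 48 and 12% at week 24, completely at random (assumed): 0.142 against 0.194. Rejection was 14.0% at week 48 and 5.2% at week 24. The t test rejected 7.6%; as it ignores the model covariance and the missingness was random, simulation error is the likely reason.
- Compound symmetry true, same missingness: 4.8% at week 48.

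**The case against.** **The t test comes first.** This stands. It uses the observed variance of each change score, so the mixed-model covariance cannot distort it. A reader might infer that Aim 1B as a whole has an inflated error rate; the article does not support that. What remains is the adjusted model. It is not a side analysis: it carries the site and wave adjustment and the missing-data handling, its interaction estimates are to be reported with intervals and P values, the Aim 2 moderator terms are added to the Aim 1A models, and a similar approach serves the secondary outcomes.

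**The 24-week primary endpoint.** A reader might infer that it is harmed too, because women are selected on poor control or a past exacerbation and baseline may therefore correlate less with follow-up. Holding all variances equal, baseline correlations of 0.4-0.5 against 0.7 between follow-ups would give 8-9% error at 24 weeks. But selection that lowers the baseline correlation also shrinks the baseline variance. Take compound symmetry (0.5-0.7) and apply the linear selection formula V − (1 − k)ss′, where s is the covariance with baseline and k, from 0.3 to 0.7, is the fraction of baseline variance left. True/model variance is then 0.90-0.98 and the error 3.9-4.7%, slightly conservative. Decay of 0.7-0.9 leaves week 24 at 4.5-5.1%. No harm to the primary contrast is shown.

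**The size is assumed.** This also stands. Constant correlation gives no bias, and a smaller 48-week variance can offset it.

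**Assumptions will be examined, and an SAP may say more.** The article does promise to examine assumptions, but names no alternative if this one fails. A serial or heterogeneous residual could be added to a random intercept, and the restriction would then not hold. However, the article does not leave the within-woman structure open: it names a restrictive one.

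**Conclusion.** The point holds in a limited form. As written, with ordinary independent residuals, the mixed model gives the 48-week contrast too small a standard error whenever ACQ correlation declines with time apart and variances are about equal. Under the patterns tried, the nominal 5% becomes about 7-9% with mild decay or visit-level noise, and 11-14% with pure exponential decay of 0.7-0.9 per 12 weeks. The 12-week standard error is then too large. The 24-week contrast is nearly unaffected, and the first-listed t tests do not depend on this covariance at all. The direction follows from algebra; the size rests on correlations that the article does not report.

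**What to change.** Replace the random-intercept-only structure with an unstructured within-woman covariance over the four visits: 4 variances + 6 covariances = 10 parameters, against 224 women. It contains compound symmetry as a special case, so little is lost if the simple structure turns out to be right. State in advance that, if it does not converge, the model reverts to a random intercept with robust standard errors. Carry the change through to the moderator models and, where the outcome is continuous, to the secondary outcomes.

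The cost is about one line of SAS or R code and a small risk of non-convergence. The fallback has a limit: robust standard errors repair the interval, but with dropout the estimate still leans on the simpler covariance. The article reports 76 women recruited at submission and completion expected in 2027, so the change can be fixed before outcome data are analysed.

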For aim 2, we will explore the potential mediation effects of multiple variables on the relationship between the intervention and clinical outcomes. That is, a portion of the intervention effect on an outcome may be going through the path via a mediator indirectly. Through mediation analysis, the direct effect, the indirect effect also known as the mediated effect, and their total effect will be measured using the approach by Yu et al [46,47] along with their CIs via bootstrapping. The multiple mediators of interest here include social support, self-regulation, self-efficacy, and PA, while the clinical outcomes of interest are the ACQ score and mini-AQLQ score. To avoid the problem of mediation analysis with cross-sectional data, we define the mediation relationship generally noted as *X*-*M*-*Y*, using *X_BL_* as the exposure at baseline, *M_j_*_,24w_ as the *j*th mediator at 12 weeks (*j*=1,…, 6), and *Y*_k,48w_ as the *k*th outcome at 48 weeks (*k*=1,2) [48]. As a secondary analysis, multilevel mediation analysis using the method by Yu and Li [49] will also be considered. For moderation analysis, we will examine moderators including comorbid conditions (depression and obesity), social determinants of health (age, income, and education level), asthma severity (mild, moderate, and severe), and neighborhood environment (walkability and safety) by separately adding their interaction terms with the treatment group to the models mentioned for aim 1A to estimate their moderating effects on treatment responsiveness. We will focus on several plausible behavioral mechanisms. We anticipate improved PA will lead to improved asthma outcomes (control and quality of life) and a reduction in self-reported exacerbations and emergency health care use.

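### The moderation term named for Aim 2 omits time, so it estimates an average over all four visits, baseline included, rather than moderation of the response at week 24

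*Protocol article*

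**What the plan says.** The Data Analysis Plan compares the change in ACQ between arms with a t test and then fits a regression: "A linear mixed model with a subject-level random intercept". The response in that model is the ACQ score at each visit, not its change, and the fixed effects are described as "having time (12 weeks vs baseline; 24 weeks vs baseline; 48 weeks vs baseline), group (ACTION vs education control), and their interaction". Baseline is therefore a response row, and the section says that the model will "estimate the efficacy of the intervention through the interaction terms", which means group-by-time.

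For Aim 2, the same section examines each moderator by "separately adding their interaction terms with the treatment group to the models mentioned for aim 1A". The purpose it gives for doing so is "to estimate their moderating effects on treatment responsiveness". It names no term that involves moderator, group and time together.

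Three other statements bear on this:
- Study Design: "The primary efficacy end point is a change from baseline to week 24 asthma control".
- Study Design also places assessments at weeks 0, 12, 24 and 48, and singles out week 48 as important for contextual moderators, among other things.
- Contextual Moderators: these variables are collected at baseline, so each is fixed over a woman's four visits.

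**The concern.** A moderator-by-group term with no time component is a single number applied to every visit. One of those visits is baseline, before treatment, where no treatment effect can exist and so none can be moderated. The term therefore describes how the difference in ACQ level between arms, averaged over the study, varies with the moderator. The stated target is responsiveness, and in this model response is change from baseline, carried by group-by-time. Moderation of response is then moderator-by-group-by-time.

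The same term is planned for every listed moderator: depression, obesity, age, income, education, asthma severity and neighborhood environment. If the averaged coefficient is reported as moderation of the week-24 response, its size will usually be understated, and a small estimate may be read as evidence that response does not differ between subgroups.

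**Working it through.** The article gives no moderation effect size, SD, correlation or power figure, so there is no published number to reproduce. The check is of what the stated term estimates.

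**Inputs from the article.** Four response visits (0, 12, 24, 48 weeks); random intercept; time, group and group-by-time as fixed effects; moderators fixed at baseline; N = 224; two-sided 0.05.

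**Assumptions, not in the article.** 1:1 allocation and a 50/50 binary moderator, hence 224/4 = 56 women per cell; SD 1 at each visit; within-woman correlation ρ of 0.3, 0.5 or 0.7; the moderator's main effect in the model; complete data.

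**Step 1: target of the stated term.** Let d0, d12, d24 and d48 be the moderator-by-group differences at the four visits. With complete data and a random intercept, a time-constant between-woman term is estimated from each woman's mean over her visits. Its target is

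(d0 + d12 + d24 + d48)/4, with d0 = 0 in expectation by randomisation.

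The quantity that matches the week-24 endpoint is d24 − d0.

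**Step 2: share of d24 recovered.**

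| Moderation at weeks 12, 24, 48, relative to week 24 | Calculation | Share |
|---|---|---|
| 1, 1, 1 (sustained) | 3/4 | 75% |
| 0.5, 1, 1 (builds, then held) | 2.5/4 | 62.5% |
| 0.5, 1, 0.5 | 2/4 | 50% |
| 0, 1, 0 (week 24 only) | 1/4 | 25% |
| 0.5, 1, 2.5 (strong late growth) | 4/4 | 100% |

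There is no shrinkage once d12 + d48 ≥ 3 × d24.

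A mixed-model simulation with true d24 = 0.50, ρ = 0.5, no dropout and 120 runs per pattern gave mean two-way estimates of 0.38, 0.35 and 0.25 for the first three rows, against targets of 0.375, 0.3125 and 0.25. The Monte Carlo standard error is about 0.211/√120 = 0.019. With 20% dropout the means were 0.33, 0.24 and 0.25. The three-way coefficient averaged 0.49 to 0.55 throughout.

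**Step 3: power.** Each contrast is a difference of differences over four cells, so SE = √(4v/56). For the two-way term, v = (1 + 3ρ)/4. For the three-way week-24 contrast, v = 2(1 − ρ). Take sustained moderation of 0.60 SD. The two-way term then targets 0.75 × 0.60 = 0.45 and the three-way contrast 0.60. Power ≈ Φ(effect/SE − 1.96).

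| ρ | Two-way SE | Two-way power | Three-way SE | Three-way power |
|---|---|---|---|---|
| 0.3 | √(4 × 0.475/56) = 0.184 | 68.5% | √(4 × 1.4/56) = 0.316 | 47.5% |
| 0.5 | √(4 × 0.625/56) = 0.211 | 56.7% | √(4 × 1.0/56) = 0.267 | 61.2% |
| 0.7 | √(4 × 0.775/56) = 0.235 | 48.1% | √(4 × 0.6/56) = 0.207 | 82.6% |

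For this pattern the two tests have equal power where 0.75²/[(1 + 3ρ)/4] = 1/[2(1 − ρ)], which gives ρ = 0.875/1.875 ≈ 0.47. For the pattern that is half-size at weeks 12 and 48, replacing 0.75 by 0.5 gives ρ = 0.25/1.25 = 0.20.

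**The case against.** The strongest reply is that this is shorthand in a condensed article. Interaction with treatment group may be meant as interaction with the treatment effect, which already includes time. The article also refers to Aim 1A models in the plural and defines the outcome as a change in ACQ; in a regression of that change, moderator-by-group would be the right term. A fuller document may hold the model statement.

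Some of this stands: the authors may well intend a three-way term. But for the change score the article describes only a t test, which has no model to extend. The one ACQ regression it describes is the repeated-measures model. The text names time in that model's interaction and leaves it out of the moderation term. This is a stated term that misses its stated target, and not merely an absent detail.

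Three stronger readings are tempting and are not supported:
- *Power is necessarily lost.* The article gives no within-woman correlation. At 0.3 the averaged term has more power under sustained moderation, because it pools four visits.
- *Attenuation of 75% is to be expected.* That requires moderation absent at week 12, present at week 24 and gone at week 48. Nothing in the article suggests this pattern.
- *Chance baseline imbalance makes the stated test invalid.* Without moderation, d0 has expectation zero and the two-way test keeps its nominal level. The three-way contrast also contains d0, with weight −1 instead of +1/4.

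**Conclusion.** The point holds as one of wrong target and diluted estimate. As written, the moderation coefficient targets the four-visit average of the moderator-by-group difference, whereas moderation of the week-24 response is d24 − d0. The shortfall is 25% under sustained moderation and 50% if moderation is half-size at weeks 12 and 48. It reaches 75% only in the extreme week-24-only case, and vanishes if d12 + d48 ≥ 3 × d24. These shares rest on complete data and on a literal reading of the text.

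The effect on power can go either way. It depends on a correlation that the article does not give, and on the assumed cell size, SD and moderation pattern.

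A reader might infer that the trial's main conclusion is at risk. It is not: Aim 2 is exploratory, and the primary week-24 comparison does not use this term. Severity: should-fix.

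**What to change.** State that each moderation test is the moderator-by-group-by-time contrast, in a model with all lower-order terms, including moderator-by-time. Test it at week 24 to match Aim 1A, and report the week-48 contrast as well, because Study Design gives that visit a role for contextual moderators. Give each contrast with its 95% CI.

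An acceptable alternative is moderator-by-group at those two visits in a baseline-adjusted model of post-baseline ACQ. It has the same target under randomisation, though the estimates will not be numerically identical, and it also deals with chance baseline imbalance.

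The cost is wording in the model statement; no data collection or sample size changes. The downside is that the three-way contrast may be less precise than the averaged term if within-woman correlation is low: at ρ = 0.3 its SE is 0.316 against 0.184 under the assumptions above. If an average effect over visits is also of interest, it can be reported as a separate quantity, defined over post-baseline visits and labelled as such.

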## Results

This project received funding in August 2022 and received institutional review board approval in July 2022. The first year of this project was focused on hiring and training staff, regulatory approvals, setting up data collection processes, and recruitment. We pilot-tested our recruitment and intervention procedures and began recruitment in April 2023. At the time of manuscript submission, 76 participants have been recruited. We anticipate study completion in 2027.

